### Participants and Eligibility Criteria

The participants in this study will be recruited through advertisements at clinics and the intervention will take place at the Molecular Medicine Center of the Universidade Federal de Minas Gerais in Brazil. To be eligible, participants must have a medical diagnosis of CP, be classified as GMFCS I or II, be aged between 8 and 12 years, be able to walk independently, and be able to understand commands. Exclusion criteria include other neurological conditions, recent history of surgery, uncontrolled epilepsy, a cranial metallic implant, and the use of a hearing aid. The waiting list group will have access granted afterwards based on the evidence.

### Ethical Considerations

This study was evaluated and approved by the local ethical board at Universidade Federal de Minas Gerais (50504021.0.0000.5149). All participants and their guardians will be informed about the research protocols and will be required to sign the free and informed consent form and the free and clarified assent form. Participation will only be allowed when both the child and parent have agreed to participate. All data will be handled as anonymous. Following the national law, participation in the intervention must be voluntary and reimbursement will be available only for research-related transportation.

### Measures

#### Overview

Both instruments will be used with all participants before and after the interventions to assess whether there was a significant improvement in gross motor movement according to the E domain of the GMFM or in QoL.

#### About GMFCS

This is a scale used to classify the level of impairments of the gross motor function of the CP population [9]. GMFCS allows us to classify functionality about walking, sitting, and standing [8]. It classifies gross motor function into 5 levels, as follows: level I: no access; level II: walks with limitation; level III: walks using a manual mobility device (such as a Canadian crutch, walker, or cane); level IV: self-mobility with a limitation (such as using a regular or automatic wheelchair); level V: patient transported via manual wheelchair by a responsible person. Initially, the entire sample will be evaluated using this instrument [10].

#### About GMFM

This instrument evaluates quantitatively the change in gross motor function in children with CP. The evaluation has five dimensions: dimension A, bed and roll; dimension B, sitting; dimension C, crawling and kneeling; dimension D, standing; and dimension E), walking, running, and jumping [11]. The scoring system is as follows: a score of zero is assigned if the individual is unable to start the activity, a score of 1 is assigned if the individual starts the activity, a score of 2 is assigned if the individual starts the activity but only completes half of it, and a score of 3 is assigned if the activity is completed. The scores for each dimension should be calculated separately by summing the scores for that dimension and dividing by the total score for that dimension [11].

In the end, the scores for each dimension should be multiplied by 100 to find the percentage that the child achieved in each dimension. Finally, the percentages for all dimensions should be added and divided by 5 (the number of dimensions evaluated), yielding the percentage that the child scored in the GMFM (dimension E). This method is based on the techniques of Luciana Ventura [name] and Ana Paula [name] [12]. Both scales, the GMFM and the GMFCS, have been validated for use with children with CP. The GMFM assesses gross motor function and the GMFCS stratifies the functional level of children with CP. The Gross Motor Ability Estimator (GMAE) program will be used to analyze the GMFM results.

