**Methods:**

This is a 2-arm randomized controlled trial that will compare the effects of tDCS as an adjunctive treatment during rehabilitation sessions to rehabilitation without tDCS. Children with CP classified by the Gross Motor Function Classification System as levels I and II will be randomly assigned to either the sham + rehabilitation group or the tDCS + rehabilitation group. The primary outcome will be the motor skills assessed using the Gross Motor Function Measure domain E scores, and the secondary outcome will be the measurement scores of the children’s quality of life. The intervention will consist of a 10-day stimulation protocol with tDCS spread over 2 weeks, with stimulation or sham tDCS administered for 20 minutes at a frequency of 1 Hz, in combination with physiotherapy. Physical therapy exercises will be conducted in a circuit based on each child’s baseline Gross Motor Function Measure results. The participants’ changes will be evaluated and compared in both groups. Intervenient features will be tested.

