According to the previous results, we hypothesized that tDCS use might improve specific motor skills and positively impact QoL in a more homogeneous population with CP. This study was designed to examine the impact of the combination of tDCS and conventional rehabilitation exercises on the improvement of gross motor function in children with CP classified as level I and II in the Gross Motor Function Classification System (GMFCS). The primary outcome measure will be assessed using the scores of the Gross Motor Function Measure (GMFM) dimension E and the secondary outcome is the children’s QoL.

According to Castelli and Fazzi [7], rehabilitation is a complex process that aims to promote the best possible participation and QoL for the child and the family. Rehabilitation for children with CP must be timely, intensive, and family-centered [7]. Despite the importance of understanding the effects on children’s QoL, QoL is not commonly measured.

Castelli and Fazzi [7] recommend intensive rehabilitation with trained professionals and a multidisciplinary team focused on the child’s functional improvement. Rehabilitation is one of the main parts as it involves performing functional assessments, establishing a functional prognosis, constructing a rehabilitation plan, and promoting a multidisciplinary approach [7].

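### The scoring rule averages all five GMFM dimensions and labels the result dimension E, so the primary outcome as computed differs from the one declared

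*Protocol article*

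**What the plan says.** The declared endpoint is consistent across the article. The abstract (Methods) states: "The primary outcome will be the motor skills assessed using the Gross Motor Function Measure domain E scores". The Introduction repeats it: "The primary outcome measure will be assessed using the scores of the Gross Motor Function Measure (GMFM) dimension E". The Measures overview says the instruments will show whether there was "significant improvement in gross motor movement according to the E domain of the GMFM or in QoL". The Discussion again names dimension E as primary and quality of life as secondary.

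The calculation is given only under About GMFM. That section lists five dimensions, A to E, with E covering walking, running and jumping. Each dimension's item scores are summed and divided by that dimension's total, and then "the scores for each dimension should be multiplied by 100 to find the percentage that the child achieved in each dimension". The last step takes the percentages of all dimensions, which are "added and divided by 5 (the number of dimensions evaluated), yielding the percentage that the child scored in the GMFM (dimension E"). The section closes with a further tool: "The Gross Motor Ability Estimator (GMAE) program will be used to analyze the GMFM results".

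**The concern.** The final scoring step and its label contradict each other within one sentence. A mean over lying and rolling, sitting, crawling and kneeling, standing, and walking, running and jumping is a whole-instrument score, not dimension E. Because the label gives that mean the name of the primary outcome, an analyst who follows the text literally would compute the mean and report it as dimension E.

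Two things are at stake. First, the reported primary result could be an estimate for a different variable, with three of its five components describing abilities below walking in children who must walk independently to be eligible. Second, the article would support either the dimension E percentage or the five-dimension mean as the primary score, and it leaves the role of the GMAE output unstated. A primary endpoint needs a single definition, fixed before the data are seen.

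**Working it through.** **1. The plan's own figure.** Sample Size gives 176 in total (88 per group) for effect size 0.5, power 0.95 and alpha 5%. A two-sample t-test with 1:1 allocation needs 87.3, so 88 per group, if one-sided, which matches. Two-sided it needs 104.9, so 105 per group (210 in total), which does not match. The article does not state sidedness. The calculation uses only a standardised effect and names no outcome, SD or raw-point difference. It therefore does not show which GMFM score was intended, and 176 does not change under the correction below.

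**2. Declared outcome against scoring rule.**
- Declared: E% = 100 x (sum of E item scores / maximum E score). About GMFM produces this as an intermediate step.
- Final step as written: T = (A% + B% + C% + D% + E%) / 5, labelled dimension E.
- T equals E% only if E% happens to equal the mean of the other four percentages.

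**3. Weight of E in raw points.** The change in T is (dA + dB + dC + dD + dE) / 5, so E has weight 1/5. Take assumed starting values A = B = C = 100, D = 90, E = 70:
- T = (100 + 100 + 100 + 90 + 70) / 5 = 92.0.
- Raise E by 10 to 80: T = (100 + 100 + 100 + 90 + 80) / 5 = 94.0. Ten points in E become 2 points.

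The factor of five belongs to an effect confined to E. If D also moves, T moves more:
- dE = 10, dD = 5: (10 + 5) / 5 = 3.0 points.
- dE = 10, dD = 10: (10 + 10) / 5 = 4.0 points.

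The section tDCS Intervention says in one sentence that the exercises target D and E. Later in that section, and in Interventions: Participants, only E is named. An effect on D can therefore be neither assumed nor excluded.

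**4. Does this settle the standardised effect?** Assume A to C are constant. Let k = Var(D)/Var(E) and rho = the correlation of D and E. Then SD(T) = SD(E) x sqrt(1 + k + 2 x rho x sqrt(k)) / 5. With an effect of 0.5 SD on E, the divisor 5 cancels:

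d(T) = (0.5 + effect on D in units of SD(E)) / sqrt(1 + k + 2 x rho x sqrt(k)).

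| Assumption | d(T) |
|---|---|
| k = 1, rho = 0.7, no effect on D | 0.5 / sqrt(3.4) = 0.27 |
| k = 0.25, rho = 0.5, no effect on D | 0.5 / sqrt(1.75) = 0.38 |
| k = 0 (D constant), no effect on D | 0.5 / 1 = 0.50 |
| k = 1, rho = 0.7, D gains as much as E | 1.0 / sqrt(3.4) = 0.54 |

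All k and rho values are assumptions; the article gives none. The result can fall below, equal or exceed 0.50. The formula is also for an unadjusted comparison, whereas Sample Size plans analysis of covariance on baseline, for which residual SDs would be needed.

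**The case against.** The strongest defence is that the intent is clear. Dimension E is named as primary throughout, the E percentage already exists as an intermediate step, and the parenthesis may be a slip attached to an ordinary description of the whole-instrument score. This is also a condensed article. The defence makes the fix easy but does not remove the contradiction: the formula and the label stand in the same sentence, it is the only scoring rule shown, and nothing elsewhere corrects it. It is a statement that is wrong as written, not a detail left to a fuller document.

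A reader might infer more than the article supports, and on these points the defence is right:
- **A fivefold loss of standardised effect, or a large loss of power.** The divisor acts on the SD as well as on the effect. With d = 0.27 or 0.38 and no effect on D, power would drop, but a constant D leaves d at 0.50 and an equal raw gain in D gives 0.54 with k = 1 and rho = 0.7. The direction is not established.
- **That the trial was sized or registered on dimension E.** The effect size of 0.5 is tied to no outcome, and the registry record is not at hand.
- **That GMAE supplies a rival primary score.** The article does not say what the program outputs. It is fair only to ask that its role be stated.

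**Conclusion.** The point holds and must be fixed, because it concerns the definition of the primary endpoint. As written, the rule produces the five-dimension mean and calls it dimension E, while the rest of the article declares dimension E itself.

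The one exact size is the weight of E, one fifth: a 10-point gain in E appears as 2 points if A to D do not change, and as more if D also improves. This follows from the stated formula, with no assumption about variances. The consequence for standardised effect size and power cannot be determined from the article, so none is claimed. The missing statement on how the GMAE output relates to the primary outcome is a lesser part of the same problem.

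**What to change.** In About GMFM:

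1. State that the primary outcome is the dimension E percentage = 100 x (sum of dimension E item scores / maximum dimension E score), analysed as the post-intervention score adjusted for baseline, as Sample Size already plans.
2. Remove the dimension E label from the five-dimension mean, call it the GMFM total score, and state that it is not primary.
3. State what the GMAE output is used for, so that it does not serve as an alternative primary score.

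The cost is wording and the computed endpoint. The item scores are already collected under the existing scoring rule, so visits, data collection and the stated sample size do not change. The correction should be made and dated before any comparison between groups is seen.

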#### About PedsQL

The PedsQL is a multidimensional tool to measure health-related QoL in children and adolescents. It is a practical scale on the dimensions of health outlined by the World Health Organization, with questions related to the frequency of problems faced in the last month. The 23 item-PedsQL has 8 items for physical functioning; 5 for social functioning; 5 for emotional functioning; and 5 for school functioning, with 15 on patients’ psychosocial health.

### tDCS Intervention

#### Overview

The IG will receive 10 sessions of tDCS with a frequency of 5 daily sessions per week, over a period of 2 weeks. The stimulation will be administered during rehabilitation sessions. The electrodes will be 35-cm^2^ sponges moistened with normal saline (0.9% NaCl solution). The stimulation will consist of anodal stimulation in the primary motor cortex (M1) and cathodal stimulation in the supraorbital region on the contralateral side, at an intensity of 1 mA and a duration of 20 minutes at a steady-state level, with a ramp-up and ramp-down of 4 seconds. The stimulation will be combined with specific exercises in a circuit format to target dimensions D and E of the GMFM [13]. CG will undergo 10 sessions of sham tDCS associated with rehabilitation activities 5 times per week, for a total of 2 weeks. Activities that target dimension E of the GMFM will be organized as a circuit including running, walking, and jumping. Any change to the trial will be informed along with the reason for the change.

#### Safety

The device used, tDCS Soterix Medical (Soterix Medical Inc), model number 1300-A and serial number 13ITC0619005, is approved by the Food and Drug Administration for use as an experimental device and some for clinical purposes (ANVISA-80969860041). Further, 3.5-cm^2^ electrodes will be used. Bikson et al [13], prove if the purpose is to modulate neurophysiological measures for resting motor cortex stimulation in healthy young people (1 mA intensity), tDCS for 4 seconds induces acute excitability alterations.

Krishnan et al [14] demonstrated adequate safety of tDCS in children and adolescents. Well-accepted threshold of tDCS current density is <142.9 A/m^2^ or 14.29 mA/cm^2^. Each patient will undergo a thorough health assessment and medications in use will be registered as well as all health conditions. Cardiac frequency, blood pressure, temperature, respiration, clinical assessment of mental and functional status, and physical examination will be measured [15]. Any apparent side effects will be registered, and all changes to the study will be described so that individuals have the option to interrupt the trial; the trial may also be suspended.

#### Adverse Effects

Adverse effects will be assessed using the tDCS adverse effects questionnaire [16]. The dropout rate will be reported, and dropout reasons will be stated [15]. tDCS is generally well-tolerated with no serious adverse events [14]. The effects reported are rare, mild, and transient, with “redness,” “slight tingling,” “itching,” and “burning sensation” as the most reported events. The intensity of current, density, and electrode size will be optimized to modulate the tingling and itch perception during transcranial stimulation. Furthermore, we will not pass the well-accepted threshold of tDCS current density (<142.9 A/m^2^ or 14.29 mA/cm^2^) [14].

### Allocation

Participants will be randomly assigned to tDCS groups with a 1:1 allocation as per a computer-generated randomization schedule stratified by the patient’s age using 5 permuted blocks of 6 participants.

### Implementation

All participants will be randomized, and the randomization will be performed by the researcher who will carry out an intervention; the others will not know which group the participant is in. This member will upload the randomization results to the institution’s REDCap (Research Electronic Data Capture) database [17]. The researcher who will perform a physiotherapeutic intervention and the researcher who will apply the assessments and questionnaires will not have information about group allocation.

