## Methods

This study is a single-blind randomized controlled trial (RCT). The participants will be blinded to the treatment allocation during the trial, but the researchers conducting this study will be aware of the treatment allocation. This study will conform to the CONSORT (Consolidated Standards of Reporting Trial) guidelines for nonpharmacological interventions. This study has been approved by the ethics committee in research.

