### Blinding

This will be a double-blinded study; during this study, the participants will be seen by three different teams: (1) the researcher who performs the assessment and questionnaires, (2) the neuromodulation team who apply the tDCS, and (3) the physiotherapist who performs the physiotherapy exercises. There will be no members working simultaneously on both teams. The results of randomization will only be available to the neuromodulation member responsible for the intervention, and the scales’ results will only be available to the researcher who performed the assessment and questionnaires. The results will be held in a different project in REDCap and will be available only to the researcher who makes the assessment and questionnaires.

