### Interventions: Participants

Initially, we will explain to the child how the intervention process will be carried out. The electrodes will be moistened in saline solution and will be placed on the participant’s head, which may cause slight discomfort as it will wet the child’s head, and, to minimize this discomfort, we will frequently dry their face. Associated with this, the child will perform physical therapy exercises.

CGs for tDCS will receive placebo stimulation for 30 seconds, for 10 sessions to give the child an initial feeling of stimulation. Associated with the placebo, the child will perform physical therapy exercises, focusing on the demands of the GMFM dimension E. The tDCS intervention will receive a current of 1 mA, for 20 minutes, for 10 sessions also associated with physical therapy exercises, focusing on the demands of the GMFM dimension E.

The intervention lasts from 25 to 35 minutes with each participant and will have a researcher exclusively dedicated to it during the intervention period for data collection. There will be 5 sessions with each participant per week over 2 consecutive weeks, with sessions taking place on weekdays and not weekends. All included participants will complete 10 sections of physiotherapy with or without tDCS stimulation. The tDCS device contains 2 electrodes, an anode, and a cathode, in the form of 2 nonmetallic sponges measuring 5×5 cm^2^, moistened with saline solution. The anode will be positioned on the M1 of the participant’s dominant hemisphere, according to the 10-20 System EEG, while the cathode will be placed on the supraorbital region of the region contralateral to the anode. In the case of the experimental group, a current will be applied to M1 for 20 minutes for neurorehabilitation.

After 10 sessions, the GMFM test will be repeated with each patient along with the PedsQL. Further, 1 researcher will carry out the intervention or the placebo with tDCS and the other researcher will evaluate the results blindly, without knowing which group is the intervention and which is the control. The use of the equipment and the evaluation will be carried out in different rooms to guarantee the researchers’ blindness. Only the researcher in charge of using the tDCS will be aware of the allocation of children between experimental and CGs.

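### The unblinded tDCS operator performs the randomisation with a fixed, published block size of six, which leaves allocation open to being foreseen, and the article contradicts itself on who is blinded

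*Protocol article*

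**What the plan says.** **Who randomises.** Protocol article, Implementation: "the randomization will be performed by the researcher who will carry out an intervention". The same section has this person upload the results to REDCap and says that the physiotherapy researcher and the assessing researcher have no allocation information.

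**Who knows the allocation.** Blinding: "The results of randomization will only be available to the neuromodulation member responsible for the intervention". Interventions: Participants: "Only the researcher in charge of using the tDCS will be aware of the allocation of children between experimental and CGs".

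**How the list is built.** Allocation gives a computer-generated 1:1 schedule, "stratified by the patient’s age using 5 permuted blocks of 6 participants". Sample Size asks for 176 children, 88 per group.

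**Who is blinded.** The opening paragraph of Methods calls the trial single-blind and says that "the researchers conducting this study will be aware of the treatment allocation". The Blinding section says "This will be a double-blinded study" and describes three separate teams, with the outcome data in a different REDCap project. Interventions: Participants adds that outcomes are evaluated blind and in a different room from the stimulation.

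**The concern.** There are two problems. They need separate remedies.

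1. *Concealment.* One role performs the randomisation, records the result, delivers active or sham stimulation and knows every earlier allocation. With a single block size that is printed in the article, that person can partly or wholly foresee the next allocation. If the same person has any influence on who enters or when, the groups may differ at entry. The planned analysis of covariance adjusts for baseline scores. It cannot adjust for unmeasured differences created by selective entry.

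2. *Contradictory blinding statements.* GMFM dimension E is the primary outcome. An assessor scores each item from 0 to 3, judging whether a child begins an activity, half completes it or completes it (About GMFM). How far such a score can be trusted depends heavily on the assessor not knowing the group, and the article gives two incompatible accounts of what the researchers know.

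**Working it through.** **Step 1. Identify the randomiser.** Implementation says the randomiser delivers an intervention, and also that the physiotherapist has no allocation information. The only remaining person who delivers an intervention is the tDCS operator. Blinding and Interventions: Participants agree, since both restrict knowledge of allocation to that operator. The randomiser is therefore the unblinded operator.

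**Step 2. The plan's own figures.** The target is 2 × 88 = 176. A two-sample t-test with effect size 0.5, power 0.95 and α = 0.05 reproduces 88 per group when one-sided (two-sided gives 105 per group, 210 in all). That is a separate matter, and nothing below depends on it. The schedule, read literally, is 5 × 6 = 30 places, which is 30/176 = 17% of the target. Covering 176 children needs 176/6 = 29.3 blocks. If five blocks per age stratum were meant, six strata would be needed (6 × 30 = 180), and the article lists no strata.

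**Step 3. Allocations known with certainty in a 3:3 block.** There are C(6,3) = 20 equally likely sequences. Once one arm is used up, all remaining places are certain, so the number of certain places is the length of the final run of identical allocations.
- At least 1 certain: 20/20 sequences.
- At least 2 certain (last two the same): 2 × C(4,1) = 8, so 8/20.
- At least 3 certain (last three the same): 2 × C(3,0) = 2, so 2/20.

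Expected number = 1 + 0.4 + 0.1 = **1.5 of 6 (25%)**. The full enumeration agrees: 12 sequences with exactly one, 6 with two, 2 with three, and (12 + 12 + 6)/20 = 1.5.

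**Step 4. Best guessing.** The strategy is to guess the arm with more places left, and to toss a coin when they are equal. Expected correct guesses = 3 + (2⁶/20 − 1)/2 = 3 + (3.2 − 1)/2 = **4.1 of 6 (68.3%)**, against 3 of 6 by chance.

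**Step 5. Other block sizes, same method.**

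| Fixed block | Certain | Best guess correct |
|---|---|---|
| 4 | 33.3% | 70.8% |
| 6 | 25.0% | 68.3% |
| 8 | 20.0% | 66.6% |

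Changing to another known block size would therefore do little. If the operator holds the schedule itself, the proportion known is 100% whatever the block size.

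**Step 6. Trial-wide count.** On the literal 30 places, 5 × 1.5 = 7.5 allocations would be certain. If all 176 children fell in complete blocks of six, the count would be 0.25 × 176 = 44. The article does not settle which applies, and incomplete blocks in each age stratum would lower the second figure.

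**Step 7. Blinding statements side by side.**

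| Section | Label | Who is aware |
|---|---|---|
| Methods, opening paragraph | Single-blind | The researchers, without exception |
| Implementation | None | The randomiser; not the physiotherapist or assessor |
| Blinding | Double-blind | Neuromodulation member only |
| Interventions: Participants | None | tDCS researcher only; assessor blind |

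The first row cannot stand with the other three.

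**The case against.** The strongest reply is that foreknowledge biases selection only if its holder can influence entry, and no section says the operator screens, obtains consent, enrols or schedules. Recruitment says that all patients who meet the criteria will be invited. Most of the eligibility criteria (diagnosis, GMFCS level, age, independent walking) leave limited discretion, and the operator does not score the baseline. A condensed article may also leave enrolment roles to a fuller document. This stands as a limit on the consequence: a reader might infer that selection bias is present, and the text does not show it. It does not remove the point, because giving the randomisation to the unblinded operator is a stated procedure and not an omission.

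A reader might also infer from the opening of Methods that the assessor is unblinded. Three later sections describe assessor blinding in concrete terms, against one general sentence that does not name the assessor. The later arrangement is clearly the intended one. The contradiction is real, but it is a fault of the text that one rewritten paragraph can cure.

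Finally, a reader might multiply 25% by 176 and report 44 allocations known in advance. That presumes about 29 complete blocks, where the article literally describes five, and it presumes that the operator infers from past allocations and does not hold the list. It can serve only as a conditional illustration.

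**Conclusion.** The point holds in two limited parts. First, as written, the unblinded operator randomises with a fixed, published block size, and nothing in the article separates that role from enrolment or scheduling. Allocation is therefore left open to being foreseen: on average 1.5 of 6 per block with certainty and 4.1 of 6 by best guess, or all of them if the operator holds the schedule. The per-block figures assume 1:1 blocks of six and knowledge of the earlier allocations in the same stratum. The consequence is a risk of selection bias, and no trial-wide number can be fixed from the article.

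Second, the single-blind statement at the start of Methods contradicts the later sections. The assessor-scored primary outcome is exposed only if that opening statement governs. Both parts should be corrected, because concealment and assessor blinding underpin the primary comparison. No sample-size figure changes.

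**What to change.** **For children not yet randomised.** Have someone who does not treat, assess or enrol children generate the list and load it into the REDCap system already in use. Release each allocation to the tDCS operator only after eligibility, consent and the baseline GMFM and PedsQL are locked. As a secondary safeguard, vary the block size at random (for example 4 and 6) within age strata and do not disclose the sizes. This costs no balance: a 3:3 block can already be 3 apart part-way through, and mixing in blocks of 4 (at most 2 apart) leaves the maximum at 3 per stratum.

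**For children already randomised.** Inclusion was planned from July 2023 to July 2024 and data collection is described as ongoing, so the change may reach only some children, or none. For the rest, report who generated the schedule, who held it and who had access to it.

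**Text.** Rewrite the opening of Methods to match Implementation, Blinding and Interventions: Participants: participants, physiotherapist and assessor blinded, and only the tDCS operator unblinded.

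**Cost.** A few hours of REDCap set-up and a short amendment. This assumes that an existing member independent of the three teams can hold the list; the article names no such role.
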